**Figure 3 F3:**
[figure not shown]
**Process evaluation plan**. The file contains an overview of the process evaluation plan.

### Economic evaluation

A cost-effectiveness analysis will be carried out in which costs will be considered from a societal perspective, which implies that all costs and effects are taken into account. The economic evaluation will be a combination of a cost-effectiveness and cost-utility analysis. The primary clinical outcome for the cost-effectiveness analysis is disability, which will be measured at baseline and at 6, 12 and 24 months follow-up by means of the GARS [34]. Within the cost-utility analysis, the primary outcome is generic health-related quality of life (QALY). Therefore utilities will be measured by means of the standard Dutch version of the EuroQol (EQ-6D) [47,48] at baseline and at 6, 12 and 24 months follow-up. Subsequently, a direct value for every state of health will be generated using the Dolan tariff [49,50], which involves an algorithm for interpolating EuroQol results to population utilities.

This study will assess intervention costs, healthcare costs and patient/family costs. Intervention costs relate to the delivery of the intervention, for example costs related to the screening procedure, time spend on intervention by healthcare professionals, travel expenses of professionals and costs for training activities. Data will be registered prospectively by the researchers. Healthcare costs relate to hospital visits (inpatient and outpatient treatment), GP consultations, visits to paramedics, prescribed medication and (nursing) home care. Data of healthcare utilization will be assessed by means of registries of health insurance agencies, GP practices and hospitals. In addition, questions about healthcare utilization are included in the postal questionnaire and the telephone interview. Patient and family costs relate to costs that are made by the patients or informal caregivers themselves and include, for example, travel expenses (based on the mean distance to and from healthcare professionals) and informal care (based on hours delivered). These data would preferably be assessed by means of a cost diary [51]. However, in the present study a diary was considered to be too burdensome for frail older people (and their informal caregivers).

In order to calculate costs, volumes of resource utilization will be multiplied by the cost price of that unit. Cost prices will be obtained from the Dutch guidelines for cost analysis in health care research [52,53]. Where such guidelines are not available for a specific category, real costs or tariffs will be used to estimate costs.

Differences in costs and effects will be presented in incremental cost-effectiveness ratios (ICERs). The ICERs represent the differences in mean costs between the intervention and usual care group in the numerator and the difference in mean effects in the denominator [54]. Sensitivity analysis will be done to assess the robustness of the assumptions we made.

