### Randomization

Cluster randomization was applied to avoid contamination bias [24-26]. Before the screening procedure started, six practices were randomly allocated to the new intervention and six practices continued care as usual. Before randomization, the GP practices were pre-stratified into four strata on the basis of practice characteristics, which may influence the results of the study:

1. number of older patients in the practice (< 350 patients versus ≥ 350 patients);

2. urban versus rural area.

It is assumed that GPs working in a practice with a large number of older patients have more experience with geriatric care. Furthermore, it is expected that older people living in a rural area have more support from the informal care system than people living in an urban area.

The practices were stratified in pairs and randomized into either intervention or control group using a computer generated randomization list. To promote extrapolation of the results, practices settled in an urban area with a large number of older people had twice the chance of being allocated to the intervention group than practices in the other three strata.

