#### Secondary outcome measures

Secondary outcomes are depressive symptomatology (depression subscale Hospital Anxiety and Depression Scale) [35], social support interactions (Social Support List - Interaction version) [36], fear of falling (Short Falls Efficacy Scale - International) [37] and social participation (Maastricht Social Participation Profile) [38]. Feelings of loneliness will be assessed by the question: "During the past 4 weeks, how often did you feel lonely?" [19]. The frequency of falls will be assessed by the question: "How often did you fall during the past 6 months/12 months" [19]. Mortality, healthcare utilization and related costs will be continuously registered during 24 months.

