### Statistical analysis

Descriptive techniques will be used to describe the study groups. Baseline variables will be compared to detect differences between the intervention and control groups at the start of the study. Data of the effect evaluation will be analysed according to the intention-to-treat principle. Analysis of primary and secondary endpoints will be performed using relevant univariate, multivariate and multilevel techniques including mixed-effects regression models. A subgroup analysis will be performed for frailty status and feelings of competence and control (mastery), as these variables are assumed to be potential effect modifiers. The software package SPSS for Windows, version 17.0., will be used for all statistical analyses. The level of statistical significance will be set at 0.05 (two-tailed).

Data on the process and economic evaluation will be analysed and presented using descriptive techniques and appropriate statistical testing. Data gathered from interviews (process evaluation) will be analysed using descriptive techniques.

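### The economic evaluation is given its own analysis rule with no stated allowance for randomisation stratum or practice clustering, although the design makes both matter for incremental costs and effects

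*Protocol article*

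**What the plan says.** The Economic evaluation section of the protocol article defines the ICER by group differences: "The ICERs represent the differences in mean costs between the intervention and usual care group in the numerator and the difference in mean effects" form the ratio. The only robustness step named there concerns assumptions: "Sensitivity analysis will be done to assess the robustness of the assumptions we made".

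The Statistical analysis section has two separate sentences:
- For effects: "Analysis of primary and secondary endpoints will be performed using relevant univariate, multivariate and multilevel techniques including mixed-effects regression models".
- For economic data, in one sentence shared with the process evaluation: "Data on the process and economic evaluation will be analysed and presented using descriptive techniques and appropriate statistical testing".

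The Randomization section describes 12 practices, six per arm, in four strata formed by number of older patients and by urban or rural area. It says that these characteristics may affect the results. Allocation was not uniform over strata: "practices settled in an urban area with a large number of older people had twice the chance of being allocated to the intervention group", compared with the other three strata.

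The Sample size section says that correlation within practices raises the standard error of the treatment effect. It assumes an ICC of 0.05 and a design effect of 1.7273.

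**The concern.** Cost-effectiveness is a headline objective, and the impact on healthcare use and costs is the third stated aim. The two design features that an analysis must respect are acknowledged elsewhere in the article but are not carried into the economic rule.

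- **Stratum.** When the chance of intervention differs by stratum and the stratum is prognostic, an unadjusted difference between arms is biased in expectation, not merely imprecise. The reasons given for stratifying are experience with geriatric care and informal support. Both bear on costs, and informal care is itself a costed item.
- **Practice.** Costs and utilities of people in one practice share the same professionals and local services. Only 12 units were randomised. A test or interval that treats individuals as independent overstates precision.

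At stake is a cost-effectiveness conclusion that partly reflects practice mix and looks more certain than it is.

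**Working it through.** **1. Which outcomes the multilevel sentence reaches**

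| Economic component | Listed as primary or secondary endpoint? |
|---|---|
| GARS | Yes, primary |
| Healthcare costs | Unclear: under secondary outcomes in the text, but Table 1 puts healthcare utilization under additional measures |
| QALY from EuroQol | In neither the secondary outcome text nor Table 1 |
| Intervention costs; patient and family costs | In neither |

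Total societal cost and QALYs therefore fall under the economic sentence alone.

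**2. The plan's own figures** (difference 2.0, SD 4.5, two-sided alpha 0.05, power 80%)
- n per group = 2 × (1.96 + 0.84)² × 4.5² / 2.0², which rounds up to 80, as stated.
- Drop-out: 80 × 1.3 = 104, as stated.
- Clustering: 104 × 1.7273 = 179.6, so 180, as stated.

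The design effect is taken as given here. At ICC 0.05, the formula 1 + (m − 1) × ICC returns 1.7273 only for m = 1 + 0.7273/0.05 = 15.5, not for the planned 30 per practice (2.45). That is a separate matter, so two values are shown below.

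**3. Cost of ignoring practice**

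Completers: 180 × 0.7 = 126 per arm, or 126/6 = 21 per practice. With design effect DE, true SE / naive SE = √DE, and a naive 95% interval covers 2Φ(1.96/√DE) − 1.

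| Scenario | DE | SE ratio | Coverage |
|---|---|---|---|
| Plan's design effect | 1.7273 | 1.31 | 86% |
| ICC 0.05, 21 per practice: 1 + 20 × 0.05 | 2.00 | 1.41 | 83% |
| Assumed ICC 0.01, 21 per practice | 1.20 | 1.10 | 93% |
| Assumed ICC 0.10, 21 per practice | 3.00 | 1.73 | 74% |

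The last two rows are an assumed range, because the article gives no ICC for costs or utilities.

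On the GARS scale the naive SE is 4.5 × √(2/126) = 0.57. It becomes 0.57 × 1.31 = 0.75 at the plan's design effect and 0.57 × 1.41 = 0.80 at 2.00.

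**4. Cost of ignoring stratum**

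With practices of equal size, the bias in the incremental cost = (share of large urban practices in the intervention arm − share in the control arm) × cost gap between large urban and other practices. Stratum counts are not given, so two splits are assumed:
- Three large urban practices split 2:1: 2/6 − 1/6 = 0.17.
- Six split 4:2: 4/6 − 2/6 = 0.33.

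The second case matches a literal doubling of the chance: 4/6 for large urban practices against 2/6 for the rest. The first is 2:1 within the stratum, where the other nine split 4:5. Of every EUR 1,000 of true stratum gap, about EUR 167 to 333 would appear as incremental cost. The size of the gap itself is unknown.

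**The case against.** The strongest reply is that the article is brief rather than wrong, and several stronger readings do fail.

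- A reader might infer that the economic analysis is purely descriptive. The Statistical analysis section also announces statistical testing.
- A reader might infer that the ICER uses raw arm means. The sentence is the ordinary definition of an ICER and fits adjusted differences equally well.
- A reader might infer that clustering will be ignored. Nothing says so. GARS is the primary endpoint, so multilevel analysis is planned for it, and the secondary outcomes text says "Mortality, healthcare utilization and related costs will be continuously registered during 24 months", which arguably brings healthcare costs under the same sentence.
- A reader might point to the instability of the ratio. If the observed GARS difference were 2.0, then with 10 degrees of freedom (multiplier 2.228) its interval runs from 0.34 to 3.66 at the plan's design effect, about 11-fold, or from 0.21 to 3.79 at a design effect of 2.00, about 18-fold. This is sampling error inherent in the trial. Better modelling would not remove it, so it does not measure the harm of this fault.
- Net benefit, acceptability curves and the choice of interval method are details that an article may leave to a fuller plan. Their absence is no finding.

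It is also fair that the stratum issue reaches beyond the economic evaluation, since the article states no stratum adjustment for any analysis.

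What remains is that the article does state a rule for economic data, separate from the multilevel rule. It leaves QALYs and two of the three cost categories outside any endpoint list, and so does not commit the economic analysis to the two features that the design requires.

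**Conclusion.** The point holds as an analysis rule that needs tightening, not as proof of a naive analysis. Followed as written, the economic rule permits a difference confounded by stratum and intervals that take no account of 12 clusters.

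The loss of precision would be material at the plan's own design effect, and larger at ICC 0.05 with 21 completers per practice. Both figures carry an ICC assumed for the GARS sample size over to costs and QALYs. The coverage figures use a normal approximation. The stratum share rests on assumed splits and equal practice sizes, and its size in euros cannot be derived from the document.

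The change should be made because cost-effectiveness is a stated objective and the remedy uses data already planned.

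**What to change.** In the Economic evaluation and Statistical analysis sections, state that:
1. Incremental costs, GARS and QALYs are estimated from models with practice as a random effect, and with randomisation stratum and the baseline value (baseline GARS or baseline utility) as covariates.
2. The ICER is built from these adjusted differences.
3. Its uncertainty is obtained by modelling or resampling practices, not individuals.

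Stratum should be entered so that it identifies the large urban group, because that is where the allocation chance differed.

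Cost: plan wording and modest extra programming. No new data are needed, since GARS and EuroQol are collected at baseline. Intervals will be wider. With 12 practices in two arms, 12 − 2 = 10 degrees of freedom are available between practices, and fitting all four strata uses three of them.

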### Sample size

The population sample size is based on the primary outcome measure of disability. Based on a previous study [19], we expect to demonstrate a difference in disability between the mean change score of the intervention and the control group of at least 2.0 points on the Groningen Activity Restriction Scale (GARS) [34] (which is equivalent to an effect size of 0.44 with SD 4.5). Based on a power of 80% and an alpha of 0.05 (two-sided testing), this leads to a minimal sample size of n = 80 per group (160 in total). Based on an expected drop-out rate of 30%, the required sample size would be n = 104 per group (n = 208 in total). However, the cluster randomized design of this study has consequences for the sample size and power. Scores of individuals within a cluster are assumed to be correlated in contrast to those of individuals between clusters. A within-cluster correlation leads to a greater homogeneity of individuals within a cluster, which increases the standard error of the estimate of the treatment effect. This may result in a loss of power for detecting differences between the intervention and control group. Therefore, an Intra Cluster Correlation (ICC) coefficient is needed to determine a corrected sample size [55]. In earlier intervention trials among GPs, ICC values between 0.03 and 0.06 were used [56-58]. In the present study an ICC value of 0.05 was estimated, resulting in a design effect of 1.7273. Based on the expected drop-out rate of 30%, the required sample size is n = 180 per group (n = 360 in total, an average of n = 30 per GP practice).

According to Puts and colleagues [59], the prevalence of frailty in Dutch older people aged 55 to 85 years old varies from 12% to 21%. We have conservatively estimated that 15% of the screened population will fulfil all criteria. A response rate on the postal screening of at least 65% was expected among older people [19,60]. On average, 300 screening questionnaires per GP practice (3,498 in total) were sent to older people to obtain a sufficient number of frail older people for the trial (n = 360). In addition, (central) informal caregivers will be included as well. It is expected that a central informal caregiver will be identified for 80% of frail older people.

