## Methods/design

### Study Design

All general practitioner (GP) practices in the region of Sittard (the Netherlands) and its surroundings were invited to take part in the study, with the restriction that they had no current active and systematic policy for the detection and follow-up of frail older people. In total, 24 GP practices were interested, of which 12 were randomly selected for the study. Cluster randomization was applied to allocate the selected practices to the intervention group (six practices) or the care as usual group (six practices). A flow diagram of the study design is shown in Figure 1.

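### The 80% power claim makes no allowance for having only six practices per arm; with about 10 degrees of freedom, power is at best about 72%

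*Protocol article*

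**What the plan says.** The target in the Sample size section is a difference in mean change of "at least 2.0 points on the Groningen Activity Restriction Scale (GARS", described as "equivalent to an effect size of 0.44 with SD 4.5". For individuals, the section starts from "a power of 80% and an alpha of 0.05 (two-sided testing), this leads to a minimal sample size of n = 80 per group". Drop-out comes next: "Based on an expected drop-out rate of 30%, the required sample size would be n = 104 per group (n = 208 in total". An ICC of 0.05 is then said to give a design effect of 1.7273, after which the "required sample size is n = 180 per group (n = 360 in total, an average of n = 30 per GP practice".

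The number of randomised units is in the Study Design section: randomisation was used to "allocate the selected practices to the intervention group (six practices) or the care as usual group (six practices". The Randomization section gives the same six and six. The Statistical analysis section plans multilevel and mixed-effects models at a two-tailed 0.05 level.

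**The concern.** A design effect enlarges the standard error to reflect similarity of patients within a practice. It does not allow for the between-practice variance having to be estimated from only 12 practices. With six practices per arm that estimate has about 12 − 2 = 10 degrees of freedom, so the two-sided 5% critical value is 2.228 rather than 1.96. The calculation multiplies 80 up to 180 but keeps the quantiles of a trial with unlimited clusters.

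The stake is the meaning of a null result. The Background says that few interventions have shown benefit on disability, so a null result is plausible. The plan sets the chance of missing a true 2.0-point difference at 20%. If the real chance is nearer 28%, or higher, the stated power overstates what a null result excludes.

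**Working it through.** **Inputs, all from the Sample size section unless noted.** Difference 2.0; SD 4.5; two-sided alpha 0.05; power 80%; drop-out 30%; ICC 0.05; design effect 1.7273; 180 per group; 30 per practice. Six practices per arm (Study Design; Randomization).

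**1. Reproduce the plan.**
- Individuals: n = 2(1.96 + 0.8416)² × (4.5/2.0)² = 79.5, rounded up to 80.
- Drop-out: 80 × 1.3 = 104.
- Clustering: 104 × 1.7273 = 179.6, rounded to 180.

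The chain reproduces, with normal quantiles throughout and no term for the number of practices.

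**2. Power on the plan's effective size.** Undoing its own factors gives 180/(1.3 × 1.7273) = 80.2, so take 80 effective participants per group.
- Standard error: 4.5 × √(2/80) = 0.7115.
- Noncentrality: 2.0/0.7115 = 2.81.
- Normal reference (cut-off 1.96): power 80.3%.
- Noncentral t, 10 df (cut-off 2.228): power 71.7%.
- Detectable difference: 80% power on 10 df needs a noncentrality of 3.11, so 3.11 × 0.7115 = 2.21 points.

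**3. Why this is a best case.** With equal practice size m, the design effect is 1 + (m − 1) × ICC.
- The stated 1.7273 implies m = 1 + 0.7273/0.05 = 15.5, not 30.
- At m = 30 it is 1 + 29 × 0.05 = 2.45.
- At 21 completers per practice (30 × 0.7) it is 1 + 20 × 0.05 = 2.00.

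| Scenario | Effective n per group | Power, normal | Power, t(10) | Detectable difference, t(10) |
|---|---|---|---|---|
| Plan's effective n granted | 80 | 80.3% | 71.7% | 2.21 |
| 30 per practice, no drop-out | 180/2.45 = 73.5 | 76.8% | 68.1% | 3.11 × 0.7425 = 2.31 |
| 21 per practice, 30% drop-out | 126/2.00 = 63 | 70.3% | 61.5% | 3.11 × 0.8018 = 2.49 |

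A simulation of a practice-level t-test agrees: 68.0% at 30 per practice and 61.4% at 21.

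**4. Separate the causes.** Within each row, moving from the normal to the t reference costs about 9 points. From the first row to the last, the normal-reference figure falls from 80.3% to 70.3%. Those 10 points come from the drop-out step (multiplying by 1.3 rather than dividing by 0.7) and from the mismatched design effect. They are distinct problems and are not part of the degrees-of-freedom loss.

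**The case against.** **The quoted figure is correct for its own step.** A reader might infer that n = 80 is miscalculated. It is not. For individually randomised people, an ordinary t-test with 80 per group has 79.8% power. The fault enters later, when that figure is scaled to 180 for a design with 12 practices.

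**72% is not the power on all the plan's inputs.** This stands. ICC 0.05, 30 per practice and a design effect of 1.7273 cannot all hold. The 72% grants the plan its effective size, and removing that concession lowers power.

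**The 61% bundles other faults.** This also stands, so only about 9 points are charged to the degrees of freedom.

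**The test may be specified elsewhere.** A reader might go further and say that the trial will exceed its 5% level. A 1.96 cut-off on 10 degrees of freedom would have a type I error of about 7.8%, but the article names no reference distribution, and an article may leave that to the SAP. Likewise, the article does not say that the four strata will be fitted, so a figure on fewer than 10 degrees of freedom is not supported. The power point survives: 80% power together with a true 5% level is not delivered by this calculation, whichever reference is later chosen.

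**Modelling could recover power.** Baseline adjustment or repeated measures might help, but the Sample size section claims no such gain, and repeated measurements add no practices.

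**Conclusion.** The point holds as a missing small-cluster allowance in the sample size calculation, not as an arithmetic slip. At a true two-sided 5% level, power for 2.0 GARS points is about 72% with the plan's effective size granted, about 68% with 30 per practice and no drop-out, and about 61% with 30% drop-out. The detectable difference runs from about 2.2 to about 2.5 points. About 9 points of power are lost to the degrees of freedom in each case.

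The figures assume SD 4.5, ICC 0.05, equal practice sizes and 10 degrees of freedom. Unequal sizes would lower them further; the article gives no measure of that variation, so no figure is attached. The point is worth correcting because the stated power frames how the primary result is read. It does not invalidate the design.

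**What to change.** In the Sample size section, at the sentence giving 180 per group:

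1. Reconcile the design effect with the practice size actually planned, and with the drop-out assumption.
2. Restate the power and the detectable difference for 360 participants in 12 practices, using a t reference on practice-level degrees of freedom.

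If 21 completers per practice and ICC 0.05 are retained, the restated figures would be about 61% power and about 2.5 points. The 72% should not simply replace the 80%, since it still rests on 1.7273. The degrees-of-freedom method for the analysis may be left to the SAP, but it should match the one used for the restated power.

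The cost is a sentence or two and a less favourable stated power. No extra participants are needed.

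### The 30% drop-out allowance multiplies by 1.3 instead of dividing by 0.7, so 360 participants leave fewer completers than the plan's own calculation requires

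*Protocol article*

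**What the plan says.** The Sample size section of the protocol article builds the target in three steps.

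1. **Individually randomised size.** The difference in mean change is "at least 2.0 points on the Groningen Activity Restriction Scale (GARS"), "which is equivalent to an effect size of 0.44 with SD 4.5". From this: "Based on a power of 80% and an alpha of 0.05 (two-sided testing), this leads to a minimal sample size of n = 80 per group".
2. **Drop-out.** "Based on an expected drop-out rate of 30%, the required sample size would be n = 104 per group (n = 208 in total").
3. **Clustering.** In the plan's words, "an ICC value of 0.05 was estimated, resulting in a design effect of 1.7273". The final statement again rests on the same loss: "Based on the expected drop-out rate of 30%, the required sample size is n = 180 per group", which is 360 in total, or 30 per practice on average. The Abstract repeats the total of 360.

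The section does not define drop-out as anything other than a share of those enrolled.

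**The concern.** To finish with a required number of completers when a proportion *d* of those enrolled is lost, the required number is divided by (1 − *d*). Multiplying by (1 + *d*) gives too small a number, and the gap widens as *d* grows. At 30% the two factors are 1.43 and 1.30, so the choice matters. The stated 104 looks like the product.

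If so, the plan's 80% power does not hold at the loss the plan itself expects. That expectation should be taken seriously: participants are frail, aged 70 or over, and followed for 24 months. A reader of a null result would rely on the claim of 80% power at 30% loss.

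**Working it through.** **Inputs (all from the Sample size section):** difference 2.0 points; SD 4.5; two-sided alpha 0.05; power 80%; equal groups; drop-out 30%; design effect 1.7273.

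**Reproducing the plan's figures**

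- Base size: n = 2 × (1.96 + 0.8416)² × 4.5²/2.0² = 79.5, so 80 per group. This matches the plan.
- Drop-out, tried both ways:
  - 80 × 1.3 = 104, an exact match.
  - 80/0.7 = 114.3, so 115, no match.
- After the design effect, tried both ways:
  - 104 × 1.7273 = 179.6, so 180, a match.
  - 80 × 1.7273/0.7 = 197.4, so 198, no match.

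Only multiplication by 1.3 returns the printed 104 and 180.

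**What the stated sizes leave after 30% loss**

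| Stage | Enrolled per group | Completers (× 0.7) | Completers needed |
|---|---|---|---|
| Before clustering | 104 | 72.8 | 80 |
| After clustering | 180 | 126 | 80 × 1.7273 = 138.2 |

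The final shortfall is 138.2 − 126 = 12.2 completers per group, about 9% of what is needed.

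**Enrolment needed**

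- Before clustering: 115 per group, 230 in total.
- With the plan's design effect: 198 per group, 396 in total, which is 36 more than stated. Rounding up at each step (115 × 1.7273 = 198.6) gives 199 per group, 398 in total.

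**Power of 360 at 30% loss, with the plan's design effect**

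- Effective n per group = 126/1.7273 = 72.9.
- Standardised difference = 2.0/4.5 = 0.4444.
- 0.4444 × √(72.9/2) = 2.684; 2.684 − 1.96 = 0.724; power = Φ(0.724) = 76.6%. The t-test version gives 76.0%.
- For comparison, 80 effective per group gives 80.3% by the same normal formula.

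**Loss that the stated sizes can absorb**

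- Before clustering: 1 − 80/104 = 23.1%.
- After clustering: 1 − 138.2/180 = 23.2%.

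**The case against.** The arithmetic itself is hard to dispute; the case on the other side concerns how much it matters.

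- **The effect is small.** A fall from 80% to about 77% lies within the uncertainty of the other inputs: an ICC drawn from values of 0.03 to 0.06, and a difference taken from one previous study. This is fair, and it is why the point is moderate. It does not make the printed figures consistent with each other.
- **Recruitment may cover the gap.** The Discussion's screening results imply 3,498 × 0.797 × 0.293 × 0.481 = about 393 willing people. If all were enrolled, evenly split and 30% lost, 393 × 0.7/2 = 137.6 per group would remain against 138.2 needed, so power would stay near 80% under the plan's design effect. However, the article gives neither the number enrolled nor the split by arm, and it still plans for 360. This limits the practical consequence only.
- **Drop-outs may contribute partial data.** The outcome is measured at 6, 12 and 24 months, and the Statistical analysis section plans mixed-effects models, so people lost late would not be wholly uninformative. The 77% is therefore a complete-case figure. But the sample-size calculation treats drop-outs as lost and claims no such recovery; a gain from partial data would need its own justification.
- **The 30% might mean 30% of completers.** That reading reproduces 104, but it corresponds to a drop-out rate of 23% of those enrolled, so the wording would still need correcting.

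**Conclusion.** The concern holds. The printed 104 and 180 per group come from multiplying by 1.3, and neither leaves the required completers at 30% loss. Taking the plan's base size and design effect as given, and counting drop-outs as lost, the requirement is 198 per group (396 in total) against 180 (360). Power at 360 is about 77% instead of 80%, and the tolerable loss is about 23% instead of 30%.

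These figures deliberately hold the design effect at 1.7273. Whether that value suits 30 people per practice is a separate question, but the two issues compound. With 126 completers in each group of six practices there are 21 per practice; at an ICC of 0.05 the design effect is 1 + 20 × 0.05 = 2.0 and the effective size is 126/2.0 = 63 per group. Power is then about 70% by the normal approximation, or about 62% on 10 degrees of freedom for 12 practices. Most of that further fall belongs to the design effect and the degrees of freedom, not to the drop-out step.

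**What to change.** In the Sample size section, correct 104 to 115 per group (230 in total). Then do one of the following:

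- state the power that 360 delivers at 30% loss: about 77% with the design effect as printed, or, if the design effect is revised too, about 70% (normal) and about 62% (10 degrees of freedom); or
- state that 360 tolerates about 23% drop-out at 80% power, which holds only under the printed design effect of 1.7273.

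If the text continues to give a required total at 30% loss under that design effect, the total should read 198 per group (396) instead of 180 (360), with 360 described as the planned enrolment.

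The cost is a rewording of one paragraph and a slightly less favourable stated figure. No extra enrolment and no change to the design or analysis is needed.

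### The design effect of 1.7273 does not follow from ICC 0.05 with 30 patients per practice, so 360 patients give about 70% power, not 80%

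*Protocol article*

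**What the plan says.** All the relevant figures are in the Sample size section of the protocol article.

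- The target is a difference in mean change of "at least 2.0 points on the Groningen Activity Restriction Scale (GARS"), described as "equivalent to an effect size of 0.44 with SD 4.5", with 80% power and two-sided alpha 0.05.
- Before clustering: "this leads to a minimal sample size of n = 80 per group (160 in total").
- With 30% drop-out this becomes 104 per group.
- On clustering, earlier GP trials are cited ("ICC values between 0.03 and 0.06 were used"), and then: "In the present study an ICC value of 0.05 was estimated, resulting in a design effect of 1.7273".
- The result: "the required sample size is n = 180 per group (n = 360 in total, an average of n = 30 per GP practice").

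Study Design gives 12 practices, six per arm. The section states neither the formula nor the cluster size behind 1.7273.

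**The concern.** For a given ICC, the usual design effect depends only on the number of patients analysed per cluster. The plan gives the ICC (0.05), the cluster size (30) and the design effect (1.7273), so the three can be checked against each other, and they disagree. The discrepancy is not a stray digit, because 1.7273 is the multiplier that turns 104 per group into 180.

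What is at stake is the power claim for the primary outcome. If the real design effect is larger, the trial has a higher chance of missing a true 2.0-point effect than the 20% it states. A reader who trusts the 80% would then give a null result more weight than it deserves.

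**Working it through.** **Inputs** (Sample size and Study Design sections): difference 2.0; SD 4.5; two-sided alpha 0.05; power 80%; drop-out 30%; ICC 0.05 (cited range 0.03 to 0.06); 30 enrolled per practice; 6 practices per arm. Equal practice sizes are assumed.

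**1. Reproducing the plan's chain**

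- Unadjusted n per group = 2 × (1.96 + 0.8416)² × 4.5² / 2.0² = 79.5, so 80. Reproduces.
- Drop-out: 80 × 1.3 = 104. Reproduces.
- Clustering: 104 × 1.7273 = 179.6, so 180. Reproduces once 1.7273 is taken as given.

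**2. Testing 1.7273 with DE = 1 + (m − 1) × ICC at ICC 0.05**

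| Patients per practice, m | DE |
|---|---|
| 30 (enrolled) | 2.45 |
| 21 (70% of 30) | 2.00 |
| 104/6 = 17.3 | 1.82 |
| 80/6 = 13.3 | 1.62 |

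None gives 1.7273. Solving for m gives 1 + 0.7273/0.05 = 15.5. Solving instead for the ICC at m = 30 gives 0.7273/29 = 0.025, below the range the plan cites.

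One reconstruction hits the figure exactly: the fixed-number-of-clusters form (1 − ICC)/(1 − m × ICC) with m = 9 gives 0.95/0.55 = 1.7273. Nine would be 104/12 = 8.67 rounded up, that is, one arm's patients spread over both arms' practices. This is conjecture; the document does not say how the figure arose.

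**3. Power of 360 patients at ICC 0.05**

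Effective n per arm = completers / DE. The noncentrality is (2.0/4.5) × √(effective n / 2). The t column uses 12 practices − 2 = 10 degrees of freedom.

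| Scenario | Completers per arm | DE | Effective n | Power, normal | Power, t on 10 df |
|---|---|---|---|---|---|
| 30% drop-out | 126 | 2.00 | 63.0 | 70% | 61% |
| No drop-out | 180 | 2.45 | 73.5 | 77% | 68% |

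For the first row the noncentrality is 0.4444 × √31.5 = 2.494.

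**4. Over the plan's ICC range, with 30% drop-out (m = 21)**

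| ICC | DE | Effective n | Power, normal | Power, t on 10 df |
|---|---|---|---|---|
| 0.03 | 1.60 | 78.8 | 80% | 71% |
| 0.04 | 1.80 | 70.0 | 75% | 66% |
| 0.05 | 2.00 | 63.0 | 70% | 61% |
| 0.06 | 2.20 | 57.3 | 66% | 57% |

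**5. What the design can detect or would need**

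- Detectable difference at 80% power with effective n 63: 2.8016 × 4.5 × √(2/63) = 2.25 points (normal), or about 2.5 points on 10 degrees of freedom.
- Completers needed with six practices per arm at ICC 0.05: 80 × 0.95 / (1 − 80 × 0.05/6) = 228 per arm, against 126 expected.

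**The case against.** Five points can be made for the plan.

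- **Drop-out shares the blame.** The 70% mixes two errors. Inflating as 80 × 1.3 = 104 does not protect against 30% loss; 80/0.7 = 115 would. Keeping 1.7273 and losing 30% leaves 126/1.7273 = 72.9 effective patients, about 77% power, so the drop-out step falls short by itself. This stands, and the fix must cover it. It does not rescue the design effect, since full retention with DE 2.45 also gives only 77%.
- **The shortfall depends on the ICC.** At 0.03 power is essentially 80%. That is true, but 0.03 is the favourable end of the cited range, and the plan chose 0.05.
- **The 10-df figures go beyond the plan's method.** Its n of 80 uses the normal approximation, and Statistical analysis names mixed-effects models without fixing degrees of freedom. This is fair: the like-for-like figure is 70%, and the 10-df values show the further cost of having only 12 practices.
- **Recruitment may exceed target.** The Discussion's screening rates imply 3,498 × 0.797 × 0.293 × 0.481 = about 393 willing people. If all enrolled, there would be about 23 completers per practice, DE about 2.10, effective n about 66 and power about 72%. Extra patients in the same practices help little.
- **No bias follows.** The planned multilevel techniques can handle clustering, so the estimate and type I error are not at issue. That is correct; the error is confined to the power claim.

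**Conclusion.** The concern holds. At ICC 0.05, a design effect of 1.7273 matches neither 30 patients per practice (2.45) nor 21 completers (2.00), and nothing elsewhere in the article reconciles them. With the plan's own difference, SD, ICC, drop-out and number of practices, 360 patients give about 70% power, so the type II error is about 30% rather than 20%. Allowing for only 12 practices lowers power to about 61%.

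These figures assume equal practice sizes and the stated SD of 4.5 for change scores; unequal practices would reduce power further. About 77% with full retention shows that the stated 80% fails on the design effect alone; drop-out then takes it to 70%.

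**What to change.** In the Sample size section:

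- Replace 1.7273 with the design effect for the cluster size actually used, and state that size: 2.00 with 21 completers per practice, or 2.45 with 30 analysed per practice.
- Start from the 360 enrolled rather than multiplying up from 104, so that the paragraph is consistent: 180 per arm, 126 completers after 30% loss, effective n 63.
- Restate power for a 2.0-point difference as about 70% (about 61% on 10 degrees of freedom), or restate the difference detectable with 80% power as about 2.25 points (about 2.5 on 10 degrees of freedom).
- Give the range over ICC 0.03 to 0.06: 80% down to 66% by the normal approximation, 71% down to 57% on 10 degrees of freedom.

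The cost is a rewording of one section and a less favourable power statement. Enrolment, conduct and analysis do not change.
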